#### Research-Related Injuries

Per the Code of Federal Regulations (38 CFR 17.85), the VA will provide necessary medical treatment to research participants if they are injured by participation in this research project approved by the research and development committee and conducted under the supervision of 1 or more VA employees. Except in limited circumstances, this care will be provided at the Edward Hines Jr VA Hospital. This requirement does not apply to treatment for injuries that result from a participant’s noncompliance with study procedures. The VA does not normally provide any other form of compensation for injury. The VA has not been released from liability for negligence. Participation in this research may involve risks that are currently unforeseeable.

### Statistical Analysis

#### Sample Size Justification

Our sample size was based on a power calculation for the neural TMS target identification phase of the project using a moderate effect size of 0.65 to achieve 80% power while maintaining the type I error rate at 5%. This effect size is consistent with the WHODAS 2.0 effect sizes reported in a sample of individuals with chronic conditions (0.30-0.70) [71] and a general treatment population (0.44-1.38) [72]. After accounting for an attrition rate of 20%, at least 46 participants with AUD+mTBI will be needed for the study. Thus, we hope to enroll up to 46 participants in this pilot rTMS RCT phase. As the rTMS RCT phase is a pilot study, it is not powered, but data will inform future power calculations for larger-scale studies.

#### Data Preparation

Deidentified data will be cleaned, and appropriate missing data imputation techniques will be used [73]. Multicollinearity among ARCs will be tested; highly correlated characteristics (except for one) will be removed before the final test.

#### Covariates

Covariates (eg, age, combat and deployment status, cannabis use, and nicotine dependence) will be used in the model to adjust the effect of the intervention. A bivariate analysis will be performed to test the association between each covariate and the functional disability outcome. Only statistically significant covariates will be included in the regression model.

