#### Baseline, Post–Sham rTMS, Post–Active rTMS, 2-Week, 1-Month, 3-Month, and 6-Month Follow-Up Visits

All veterans will complete the primary outcome measure: the WHO Disability Assessment Schedule (WHODAS 2.0), a self-report of functional disability. The following ARCs will also be collected as secondary outcomes: the Penn Alcohol Craving Scale, the Obsessive-Compulsive Drinking Scale, the Timeline Follow-Back (including the number of days between baseline and screening visits), and the Alcohol Craving Questionnaire. The following additional secondary outcomes will also be assessed: the Neurobehavioral Symptom Inventory, the PTSD Checklist for *DSM-5*, the Beck Depression Inventory-II, the Beck Anxiety Inventory, and the Mood and Anxiety Symptom Questionnaire. The C-SSRS will be repeated at baseline, after both sham and active rTMS treatment session 5, and at post–sham rTMS and post–active rTMS visits. We will also assess self-reported smoking status (ie, current, former, or never smoker, with never smoker defined as having smoked <100 cigarettes in a lifetime) and the Fagerström Test for Nicotine Dependence.

Finally, all female participants will complete a urine pregnancy test using a test kit at baseline and post–sham rTMS time points.

We will be using the VA REDCap (Research Electronic Data Capture; Vanderbilt University) secure web application for data collection and data entry. Data will be checked for completeness at the time of assessment and again at the time of data entry. Reasons for missingness will be documented.

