### rTMS Intervention

#### Randomization to Stimulation Site Group

Veterans with AUD+mTBI will be randomly assigned to 1 of 2 stimulation site groups: a customized site or left DLPFC. SAS 9.4 (SAS Institute Inc) will be used to develop the randomization protocol for the veterans, ensuring an equal number of participants—assigned sequentially—in each of the 2 groups. An electroencephalography (EEG) cap along with the coordinate Beam F3 method and neuronavigation will be used for each participant to maintain the single-blind design. The randomization scheme will be provided by the biostatistician to a single unblinded administrator (who will not complete any research procedures or analyses). This administrator will inform the rTMS provider of the patient’s assigned site (left DLPFC or a customized site) for rTMS treatment.

The customized site will be one of the sites depicted in Figures 1- 3- as determined by ongoing analyses.

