## Results

As of June 2025, a total of 27 veterans with AUD+mTBI who had been enrolled in the study had completed the neural target identification phase and were awaiting enrollment in the RCT phase. Data collection for the RCT phase will be initiated soon and is expected to be completed by April 2026. We expect the results of this study to be available by May 2026.

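### Covariates for the WHODAS 2.0 model are kept only if significant in this small sample, and a collinearity rule with no cutoff could reach the alcohol-related secondary outcomes

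*Protocol article*

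**What the plan says.** **Covariates.** The section says that covariates will be used in the model to adjust the intervention effect. It gives an open list of examples: age, combat and deployment status, cannabis use and nicotine dependence. Each is to be tested in a bivariate analysis against functional disability, and "Only statistically significant covariates will be included in the regression model". No significance level is given, and no time point for either the covariate or WHODAS 2.0.

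**Further candidates.** The rTMS Parameters section adds missed sessions and the time between sessions as potential covariates. Table 2 labels the nicotine dependence test a secondary outcome and schedules it at every visit from baseline to 6 months.

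**Collinearity rule.** Data Preparation says that collinearity among alcohol-related characteristics (ARCs) will be tested and that "highly correlated characteristics (except for one) will be removed before the final test". The section on the baseline to 6-month visits says "The following ARCs will also be collected as secondary outcomes", and names the Penn Alcohol Craving Scale, the Obsessive-Compulsive Drinking Scale, the Timeline Follow-Back and the Alcohol Craving Questionnaire.

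**Size.** From the target-identification phase: "After accounting for an attrition rate of 20%, at least 46 participants with AUD+mTBI will be needed for the study". For the randomised phase: "As the rTMS RCT phase is a pilot study, it is not powered". The Results section reports that "a total of 27 veterans with AUD+mTBI who had been enrolled in the study had completed the neural target identification phase" by June 2025.

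**The concern.** The covariate rule is written into the protocol, so it is not a detail left to a later analysis plan. It lets the trial's own outcome data decide which variables adjust the primary comparison. In a sample this small, a genuinely prognostic variable is kept or lost largely by luck, and an irrelevant one can enter by luck. Because the list is open and no level or time point is fixed, the analyst also chooses what is screened and how. The post-randomisation candidates are a further problem, since treatment may affect them.

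The ARC rule raises a different question. Collinearity matters for predictors, yet the Statistical Approach models concern WHODAS 2.0 and contain no ARC predictors, and neither Covariates nor Confounders lists the four measures. In the randomised phase those measures appear as secondary outcomes. A rule that removes all but one of a correlated set could therefore be applied to prespecified outcomes after the data are seen.

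The article says the pilot data will inform power calculations for larger studies, so an adjustment set picked partly by chance would carry forward.

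**Working it through.** **1. The plan's own figure.** Inputs from Sample Size Justification: effect size 0.65, power 80%, type I error 5% (two-sided assumed), attrition 20%.

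n per group = 2(1.960 + 0.842)² / 0.65² = 2 × 7.85 / 0.4225 = 37.2, rounded up to 38. Then 38 × 1.2 = 45.6, or 46. (Dividing by 0.8 gives 47.5, or 48.) So 46 is reproduced as one group of a two-group comparison, which fits its stated origin in the target-identification phase. In the randomised phase the 46 are split equally ("ensuring an equal number of participants"), about 23 per arm. The sizes that matter for the screen are N=46, N=37 after 20% attrition (46 × 0.8 = 36.8), and N=27 if only those waiting in June 2025 enter.

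**2. Chance that a covariate passes the screen.** Assume a two-sided 0.05 level, since none is stated. With true correlation r, Fisher's z gives

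P(pass) ≈ 1 − Φ(1.96 − δ) + Φ(−1.96 − δ), where δ = atanh(r) × √(N − 3).

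For r = 0.3, atanh(r) = 0.3095.
- N=46: δ = 0.3095 × 6.557 = 2.03, so P = 0.528.
- N=27: δ = 0.3095 × 4.899 = 1.52, so P = 0.329.

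The article gives no correlations, so a range is shown:

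| Assumed r | N=46 | N=37 | N=27 |
|---|---|---|---|
| 0.2 | 0.265 | 0.219 | 0.168 |
| 0.3 | 0.528 | 0.438 | 0.329 |
| 0.4 | 0.793 | 0.695 | 0.546 |
| 0.5 | 0.950 | 0.893 | 0.768 |

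If four independent candidates are all irrelevant, at least one enters with probability 1 − 0.95⁴ = 0.19. With eight it is 1 − 0.95⁸ = 0.34.

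**3. Effect on the treatment test.** Simulated 1:1 trials with a single outcome and ordinary regression (15,000 runs for type I error, 6,000 for power). Type I error was 0.047 to 0.053 under every strategy. Power at an assumed standardised difference of 0.65, with four independent candidates:

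| Setting | All prespecified | Screened | None |
|---|---|---|---|
| N=46, each r=0.3 | 0.72 | 0.63 | 0.57 |
| N=36, each r=0.3 | 0.61 | 0.52 | 0.48 |
| N=46, each r=0 | 0.55 | 0.57 | 0.58 |
| N=36, each r=0 | 0.43 | 0.46 | 0.48 |

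**4. Does this carry over to the planned model?** Only in part. Objective 1 compares within-participant changes in a mixed model. In one complete, balanced simulated data set (46 participants, three time points), adding a time-invariant covariate as a main effect left the group-by-time estimate (−0.330) and its standard error (0.350) unchanged. The precision gain in step 3 therefore reaches the planned contrast only if data are incomplete or the covariate also enters with a time interaction.

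**5. The ARC rule.** With no cutoff stated, assume 0.7 or 0.8. For a pair with true r = 0.75 at N=46, the chance that the sample correlation exceeds the cutoff is Φ([atanh(0.75) − atanh(cutoff)] × √43):
- cutoff 0.7: (0.973 − 0.867) × 6.557 = 0.69, so 0.76;
- cutoff 0.8: (0.973 − 1.099) × 6.557 = −0.82, so 0.205.

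Which measures stay thus depends heavily on a number the article does not give.

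**The case against.** Several points on the other side stand.

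- **Blinding.** A reader might infer that the model cannot be fixed before unblinding. That does not follow: the screen relates covariates to the outcome and needs no group label, and the Single-Blind Design section says the biostatistician will be blinded to group. The screen could be run and locked on pooled data.
- **Precision.** A reader might set a screened model against one adjusted for baseline WHODAS 2.0 and call the whole gap the cost of screening. The planned mixed model already uses baseline as one of the repeated responses, so that comparison credits prespecification with something the plan already has. Step 4 shows that the loss for the primary contrast may be small.
- **Endpoints.** A reader might infer that the data choose which endpoints are reported. Data Preparation does not say so. Its stated criterion is correlation among ARCs, not treatment effect, and the Introduction's definition of ARCs includes AUD duration, which is not a trial endpoint. If the survivor were picked by its result among three or four measures correlated at 0.7 to 0.8, the false-positive rate would be about 10% to 13% instead of 5%. That is a worst case under a practice the article does not describe. WHODAS 2.0 is untouched either way.
- **Nicotine dependence.** A baseline value can be a covariate while later values are outcomes, so the double role is not itself a contradiction. What remains is that no time point is fixed.
- **Pilot status.** The randomised phase claims no power, so no stated sample size or power figure changes.

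None of this defends the screen as a way to choose covariates, or supplies the missing cutoff and survivor rule.

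**Conclusion.** The concern holds in a limited form. The Covariates section fixes a poor rule that contradicts its own opening sentence. For a moderately prognostic covariate (assumed r = 0.3, 0.05 level), inclusion is close to a coin flip at N=46 and about one in three at N=27. Type I error is not inflated in the settings examined. The cost is an adjusted estimate that depends on chance, analyst discretion over an open list, and some possible loss of precision, small for the within-participant contrast when data are complete and covariates enter only as main effects. Admitting missed sessions, session spacing or an undated nicotine measure adds the risk of adjusting for something that treatment may affect.

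The ARC rule is a lesser, separate defect. As written it could be applied to four named secondary outcomes, with no cutoff and no rule for which is kept. The article does not support the stronger claim that outcomes will be suppressed or chosen by their results. The correlations, cutoffs and effect sizes used here are assumptions, shown as ranges where possible.

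**What to change.** 1. Replace the significance screen with one or two named covariates, chosen now on prior grounds, measured before randomisation and always included. State whether each enters as a main effect only or also with time.
2. Keep baseline WHODAS 2.0 within the repeated-measures model. Do not use the post-sham score as a covariate: it appears to follow randomisation, because participants are assigned to a site and then receive sham first, and it is part of the primary contrast.
3. Keep missed sessions, session spacing and other post-randomisation variables out of the primary model. If nicotine dependence is used, specify the baseline value.
4. Delete the collinearity rule for the randomised phase, or restrict it to ARCs used as predictors, and state that all four ARC secondary outcomes will be analysed and reported.

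The cost is wording. The article describes the randomised phase as not yet started in June 2025. The downside is that a named covariate may prove weakly prognostic and cost a degree of freedom. Step 3 shows this is modest even with four worthless covariates (0.55 against 0.57 at N=46, 0.43 against 0.46 at N=36), and it is a reason to keep the list to one or two.

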#### Confounders

Variables such as depression symptoms, PTSD symptoms, anticraving medication use, and psychotherapy hours, which influence both treatment site (ie, neural target or left DLPFC) and functional disability (WHODAS 2.0), will be considered as confounders. Given a treatment site and confounders, WHODAS 2.0 scores will be calculated. The parameters of the model will be estimated by the weighted regression approach where weights will be determined by the inverse of the probabilities.

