#### rTMS Parameters

rTMS will be provided at 10 Hz, 4.9 seconds per train, intertrain interval of 30 seconds, 20 total trains per session, and an intensity of 110% MT [41,51,54]. Each patient will receive 1000 pulses per day. The sham and active rTMS sessions will each be provided daily for 2 weeks (once per d, 5 d per wk; Figure 4). If a date is missed, it will be made up as soon as possible at the end of treatment. The rates of missed sessions and durations between sessions will be recorded and used as potential covariates in analyses. rTMS procedures will be conducted by a trained TMS administrator.

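### Site is randomised, so the inverse-probability weights in the Confounders section have no systematic confounding to remove; built on values from the active block onward, they could remove part of the site effect

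*Protocol article*

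**What the plan says.** **Allocation.** Protocol article, Randomization to Stimulation Site Group: "Veterans with AUD+mTBI will be randomly assigned to 1 of 2 stimulation site groups: a customized site or left DLPFC". The scheme is generated in SAS, "ensuring an equal number of participants" in each arm. Study Design and the abstract also describe random assignment.

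**Confounders.** The list is open-ended: "Variables such as depression symptoms, PTSD symptoms, anticraving medication use, and psychotherapy hours". These are described as variables "which influence both treatment site (ie, neural target or left DLPFC) and functional disability (WHODAS 2.0), will be considered as confounders". The estimation method follows: "The parameters of the model will be estimated by the weighted regression approach where weights will be determined by the inverse of the probabilities". The section does not say what the probabilities refer to, which model is weighted, or at which visit the variables are taken.

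**Statistical Approach.** Objectives 1 and 2 each use a mixed effects model for WHODAS 2.0. Neither mentions weights.

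**When the variables are measured.** Table 2 lists the BDI-II (depression) and PCL-5 (PTSD) as secondary outcomes at baseline and at all six later visits. Under Safety Measures, participants are asked about medication changes before every TMS session. For session adherence, rTMS Parameters says: "The rates of missed sessions and durations between sessions will be recorded and used as potential covariates in analyses".

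**The concern.** A confounder of the site comparison would have to be related to site for a reason other than chance. Random assignment rules that out, so the reason given for weighting contradicts the design. The error bears on how the main comparison is estimated, and the section names the two trial arms, so it cannot be read as text left over from the target identification phase.

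The practical risk lies in timing. Weighting a randomised comparison on pre-treatment variables evens out chance differences. Weighting it on variables that treatment has already changed makes the arms alike on something the treatment did, and so removes whatever part of the effect passes through those variables. The Rationale section itself says that high-frequency stimulation has improved depression and PTSD symptoms, so these scores are plausible pathways. The RCT phase is meant to give preliminary efficacy data and to inform later power calculations, so a distorted site estimate would carry into the next trial.

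**Working it through.** **Step 1. The two sections side by side.** With random assignment to two equal groups, the probability of either site is 0.5 whatever the participant's symptoms, medication or therapy. The true inverse-probability weight is therefore 1/0.5 = 2 for everyone, which is the same as no weighting. Weights estimated from the data depart from 2 only because of chance differences, or because a variable was measured after site had begun to affect it. The article describes no stratified, adaptive or covariate-dependent allocation that would make the Confounders statement true.

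**Step 2. Which values could carry a site effect.** Everyone receives 10 sham sessions and then 10 active sessions.

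- Baseline precedes all stimulation.
- Post-sham values follow randomisation but precede active stimulation, so an effect of active stimulation at the assigned site cannot act through them.
- Values from the active block onward could carry such an effect. These include BDI-II and PCL-5 at the post-active and four follow-up visits, and therapy hours, medication changes, missed sessions and session gaps from that block on.

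**Step 3. Size if values from the active block onward are used.** The plan gives no figure for this, so it was simulated. From the plan come the enrolment target (46), the 27 veterans available in June 2025, and the effect size of 0.65 that the article uses for its sample size. Everything else is assumed:

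- Four baseline covariates X, standard normal; A = 1 for one site and 0 for the other.
- Later values M = 0.6·X + g·A + noise (SD 0.8), with g = (s, s, 0, s/2). Site shifts two symptom scores by s and therapy hours by s/2.
- Outcome = direct effect·A + 0.35·M1 + 0.35·M2 + 0.10·M3 + 0.20·M4 + noise. Within-arm SD is 1 and the total site effect is fixed at 0.65.
- Weights come from a logistic model of site on the four variables, with probabilities truncated at 0.01 and 0.99. There were 4,000 simulated trials per setting at N = 27 and 46, and 400 at N = 2000.

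The part of the effect passing through M is (0.35 + 0.35 + 0.20/2)·s = 0.80·s.

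- s = 0.3: 0.24 passes through M, leaving 0.65 − 0.24 = 0.41.
- s = 0.5: 0.40 passes through M, leaving 0.65 − 0.40 = 0.25.

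Mean estimated site effect:

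| N | Shift s (SD) | Unweighted | Weights on baseline values | Weights on later values |
|---|---|---|---|---|
| 27 | 0 | 0.66 | 0.66 | 0.66 |
| 27 | 0.3 | 0.65 | 0.65 | 0.44 |
| 27 | 0.5 | 0.66 | 0.65 | 0.32 |
| 46 | 0 | 0.65 | 0.65 | 0.65 |
| 46 | 0.3 | 0.65 | 0.65 | 0.42 |
| 46 | 0.5 | 0.65 | 0.65 | 0.28 |
| 2000 | 0 | 0.65 | 0.65 | 0.65 |
| 2000 | 0.3 | 0.65 | 0.65 | 0.41 |
| 2000 | 0.5 | 0.65 | 0.65 | 0.25 |

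At N = 46 the loss is (0.65 − 0.42)/0.65 = 35% for s = 0.3 and (0.65 − 0.28)/0.65 = 57% for s = 0.5. The N = 2000 rows match the direct effects of 0.41 and 0.25, so this is a bias that a larger sample does not cure.

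**Step 4. Cost if only baseline values are used.** No bias appears in any setting. The empirical SD of the estimate at N = 46 is 0.29 to 0.30 with or without weights. At N = 27 it rises slightly, from about 0.39 to between 0.41 and 0.42.

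**The case against.** The strongest reply is that a variable said to influence site must precede assignment, so the section's own logic, though mistaken, points to baseline values. An article may also leave measurement times to a fuller document. On that reading the weights only balance chance differences, which is legitimate in small arms and harmless for bias. This stands: it limits the consequence, but it does not repair the false statement about site or give the weights a purpose. Psychotherapy hours also fit poorly with a baseline-only reading, because they naturally accrue over time.

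The sizes above come from assumed shifts and a simple two-arm difference. Objective 1 compares sites on a difference of differences (post-active minus post-sham, against post-sham minus baseline), so the percentages do not transfer directly. The article does not say how far the two sites would differ in their effect on symptoms, or in which direction; conditioning could distort the comparison either way. This also stands.

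Missed sessions and session gaps are only potential covariates, not weighting variables. Nothing in the article shows that they depend on site, and no figure here tests them. They are a lesser part of the point, included because they can arise only after randomisation.

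Weights might be defended for dropout or for the sham-to-active order, but the section names treatment site, so neither defence rescues it.

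**Conclusion.** The statement that these variables influence site is wrong for this design, and the weights built on it have no systematic confounding to remove. That conclusion needs no assumption beyond the randomisation the article describes, together with the natural but unstated reading that the probabilities are those of site given the listed variables.

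The loss of effect is conditional. It arises only if values from the active block onward are used and site affects them. With a true effect of 0.65 SD and N = 46, it ranges from nothing (no shift) to 0.37 SD (a 0.5 SD shift).

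Three stronger readings are tempting but unsupported:

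- **The planned analysis will lose half the effect or most of its power.** The article does not say that later values enter the weights, and it claims no power for the RCT phase.
- **The standard errors will be wrong.** No variance estimator is named.
- **Allocation is not truly random.** Every description of it says that it is.

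This is a should-fix: a plain misstatement and an open choice in a pilot's main comparison, not a demonstrated bias.

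**What to change.** 1. Delete the statement that these variables influence treatment site.
2. Drop the inverse-probability weights for the randomised site comparison.
3. Estimate that comparison with the mixed effects model already given under Statistical Approach, adjusted only for prespecified pre-treatment values such as baseline WHODAS 2.0, BDI-II and PCL-5. Baseline WHODAS 2.0 is already one of the repeated measures in Objective 1, so it should not also enter there as a covariate; in Objective 2 it can.
4. Report psychotherapy hours, medication changes, missed sessions and session gaps after randomisation by arm, as description, and remove the last two from the list of potential covariates in rTMS Parameters.

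The cost is a change of analysis wording and simpler programming. Sample size, visits and measures are unaffected. According to the Results section, data collection for the RCT phase had not begun as of June 2025. If it still has not, the change can be made before any outcome is seen.
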